## Abstract

**Introduction:**

Two million out of the UK’s 5 million routine diagnostic CT scans performed each year incorporate the thoracolumbar spine or pelvic region. Up to one-third reveal undiagnosed osteoporosis or vertebral fractures. We developed an intervention, Picking up Hidden Osteoporosis Effectively during Normal CT Imaging without additional X-rays (‘PHOENIX’), to facilitate early detection and management of osteoporosis in people attending hospitals for CT scans.

**Methods and analysis:**

A multicentre, randomised, pragmatic feasibility study. From the general CT-attending population, women aged ≥65 years and men aged ≥75 years attending for CT scans are invited to participate, via a novel consent form incorporating Fracture Risk Assessment (FRAX) questions. Those at increased 10-year risk (within the amber or red zones of the UK FRAX graphical outputs for further action) are block randomised (1:1:1) to (1) PHOENIX intervention, (2) active control or (3) usual care. The PHOENIX intervention comprises (i) retrieving the CT scans using the NHS Image Exchange Portal, (ii) Mindways QCT Pro software analysis of CT hip and spine none density with CT vertebral fracture assessment, (iii) sending the participants’ general practitioner (GP) a clinical report including diagnosis, necessary investigations and recommended treatment. Baseline CT scans from groups 2 and 3 are assessed with the PHOENIX intervention only at study end. Assuming 25% attrition, the study is powered to find a predicted superior osteoporosis treatment rate with PHOENIX (20%) vs 16% among patients whose GPs were sent the FRAX questionnaire only (active control) and 5% in the usual care group. Five hospitals are participating to determine feasibility. The co-primary feasibility outcome measures are (a) ability to randomise 375 patients within 10 months and (b) retention of 75% of survivors, completing their 1-year bone health outcome questionnaire. Secondary 1-year outcomes include osteoporosis/vertebral fracture identification rates and osteoporosis treatment rates. Stakeholder acceptability and economic aspects are evaluated.

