### Sample size calculations, study power, randomisation method

Our primary intention is to evaluate the technical procedures needed for a definitive trial with fracture incidence (rather than recruitment/retention) as the primary outcome. To help set the target recruitment numbers for the feasibility study, we therefore used the surrogate outcome of osteoporosis treatment rates at 12 months follow-up to permit sufficient power to assess and conduct cross-group comparisons across trial arms within the period of recruitment to the feasibility study. Scenarios for scaling up to a definitive trial are based on previous data.^1 2 9^ Only those participants in the red/amber FRAX group (figure 4A) will be randomised, so the number of invitations needed to reach any recruitment target will also depend on the prevalence of the red/amber FRAX group. In our local preliminary application of the PHOENIX intervention in 1518 patients, the prevalence of red/amber FRAX varied between 30% at age 40 years and 50% at age 95 years (figure 4B), with overall prevalence 40.5% (95% CI 35.7% to 45.5%). There is no published UK data to compare with this but comparable prevalence was reported in a single study in the USA investigating combined bone density and fracture detection in routine CT investigations, where 42.3% (of 571 consecutive patients) were newly detected as having osteoporosis.^1^ A conservative assumption from our preliminary work is that the PHOENIX intervention will identify a further 9.6% of screened patients for treatment and that GPs will act to treat at least half of these, resulting in an expected 4.8% minimum detectable difference. If, in our study, the percentage treated at 12 months in group 2 (active control FRAX-GP arm) matches that observed in the MRC-funded osteoporosis screening Screening in the community to reduce fractures in older people (SCOOP) study^6^ (15.5%), then we would consider that an improvement in percentage treated of 4.8% would be clinically significant. Figure 4C shows the estimated total number of invitees needed to recruit the 375 red/amber risk participants, assuming different response rates and different prevalence estimates. In the scenario of 30% response (similar to SCOOP) combined with 40% prevalence of red/amber FRAX (red line in figure 4D), it would be necessary to invite a total of 3125 participants (or 625 invites per centre) to achieve the recruitment target of 375 randomised participants (75 per centre, figure 4D).

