#### Power for treatment proportions

Assuming that osteoporosis treatment percentages at 1-year follow-up in the usual care versus active control FRAX-GP versus PHOENIX intervention would be 4.5% vs 15.5% vs 20.3%, respectively (ie, as observed in SCOOP trial vs with expected improvement in PHOENIX), a total of 375 participants recruited and randomised in the ratio 1:1:1 will have 96% power (figure 4G) to detect linear trend in treatment proportions based on a two-sided test of binomial proportions at 5% statistical significance level. The same sample size will have 93% power for a secondary two-degree of freedom test of between-group contrasts in comparison with usual care. When allowing for up to 25% attrition due to non-differential dropout or incompleteness of outcomes, the remaining sample size of 280 participants will have >84% power to detect the same magnitude of differences (figure 4G).

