#### Predefined statistical analysis plan

Response rates will be calculated as the proportion of participants invited who (a) consent to take part, (b) meet eligibility criteria and (c) are randomised, with 95% CIs to assess the extent to which the realised response deviates from the expected as detailed in the power calculations above. Cumulative participant accrual over time will be plotted overall and by recruitment centre to assess any major differences in accrual and assess progress towards target. Logistic regression will be used to compare randomised groups with respect to the 12-month outcomes of treatment rates and participant retention. Baseline stratification covariates (ie, centre, sex and age) will be adjusted for in the models. Analyses will be on an intention-to-treat basis.

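### The abstract presents the study as powered for PHOENIX against active control, but that contrast has about 17% power (14% after attrition); the stated power belongs to a three-arm trend and an overall test

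*Protocol article*

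**What the plan says.** Four places in the protocol article bear on this point.

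- **Abstract, Methods and analysis:** allowing for 25% attrition, "the study is powered to find a predicted superior osteoporosis treatment rate with PHOENIX (20%) vs 16"% under active control, where the GP received only the FRAX questionnaire. The sentence then gives 5% for usual care. It quotes no power figure.
- **Sample size calculations, study power, randomisation method:** the extra patients identified by PHOENIX, halved for GP action, are described as "resulting in an expected 4.8% minimum detectable difference". If active control matches the earlier screening trial's 15.5%, "then we would consider that an improvement in percentage treated of 4.8% would be clinically significant".
- **Power for treatment proportions:** the assumed rates for usual care, active control and PHOENIX "would be 4.5% vs 15.5% vs 20.3%, respectively". On these, "a total of 375 participants recruited and randomised in the ratio 1:1:1" "will have 96% power (figure 4G) to detect linear trend in treatment proportions", two-sided at 5%. The section adds 93% for a two-degree-of-freedom test in comparison with usual care, and more than 84% for the 280 participants left after 25% attrition.
- **Predefined statistical analysis plan:** "Logistic regression will be used to compare randomised groups with respect to the 12-month outcomes of treatment rates and participant retention", adjusted for the stratification factors.

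The article gives no power for PHOENIX against active control alone.

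**The concern.** The abstract claims superiority and names active control as the first comparator. The sample size section then calls the gap between those two arms detectable. A reader who puts these together will take the trial to have adequate power to show that CT analysis adds to a FRAX form sent to the GP. The power section offers no support for that. Its two tests ask whether the three arms differ, or rise in order, and the assumed rates place most of the difference between usual care and the other two arms: 11.0 points from usual care to active control, against 4.8 from active control to PHOENIX.

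What is at stake is how the treatment results are read. A non-significant PHOENIX versus active-control comparison could be mistaken for evidence that CT analysis adds nothing. A significant trend could be mistaken for evidence that it adds something. The article says that treatment rates will inform the power calculation for a later trial, so the precision of this contrast should be described correctly.

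**Working it through.** **Inputs.** All come from Power for treatment proportions: rates of 4.5% (usual care, U), 15.5% (active control, A) and 20.3% (PHOENIX, P); 375 participants at 1:1:1, so n = 125 per arm; 280 after attrition, so n = 280/3 ≈ 93 per arm; two-sided 5%, z = 1.96.

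**1. The article's own figures.**

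With equal arms and scores 0, 1, 2, the trend statistic reduces to (P − U)/√[2p̄(1 − p̄)/n], where p̄ is the mean of the three rates. Active control enters only through p̄.

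- p̄ = (0.045 + 0.155 + 0.203)/3 = 0.1343; P − U = 0.158.
- n = 125: null SE = √(2 × 0.1343 × 0.8657/125) = 0.0431. Power = Φ(0.158/0.0431 − 1.96) = 95.6%. Using the alternative variance in the denominator gives 96.5%. Stated: 96%.
- Two-degree-of-freedom chi-square: noncentrality = 125 × Σ(pᵢ − p̄)²/[p̄(1 − p̄)] = 14.1, giving 93.0%. Stated: 93%.
- 280 participants: trend 88.6% to 90.1%; two-degree-of-freedom test 83.6%. Stated: more than 84%.

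The stated figures therefore reproduce, the last of them approximately.

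**2. The contrast named in the abstract, P versus A.**

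Power = Φ[(d − 1.96 × SE₀)/SE₁], with d = 0.203 − 0.155 = 0.048 and pooled rate 0.179.

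- n = 125: SE₀ = √(2 × 0.179 × 0.821/125) = 0.0485; SE₁ = √[(0.203 × 0.797 + 0.155 × 0.845)/125] = 0.0484. Power = Φ[(0.048 − 0.0950)/0.0484] = 16.6%, or 16.7% with the opposite tail included. Simulation gives 16.2%.
- n = 93: 13.4%, or 13.6% with the opposite tail. Simulation gives 13.6%.
- The abstract's rounded 20% versus 16%: 12.7% and 10.6%.
- One-sided 5%: 25.6% and 21.4%.

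Solving the same formula for other quantities:

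- Increase over 15.5% detectable with 80% power: about 14.8 points at n = 125 and 17.5 points at n = 93.
- Participants per arm for 80% power at 4.8 points: about 1,000.
- Expected half-width of the 95% CI for the difference, 1.96 × SE₁: 9.5 points at n = 125 and 11.0 at n = 93.

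**3. Power by contrast (same formula).**

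| Contrast | 125 per arm | 93 per arm |
|---|---|---|
| PHOENIX vs usual care | 97% | 91% |
| Active control vs usual care | 83% | 71% |
| PHOENIX vs active control | 17% | 14% |

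**4. Can the trend or overall test stand in for P versus A?** Set PHOENIX equal to active control: 4.5%, 15.5%, 15.5%.

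- 375 participants: trend power 77% to 79% by formula (80% by simulation); two-degree-of-freedom test 80% by formula (87% by simulation).
- 280 participants: 64% to 66% and 67% by formula.

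Either test would usually be significant although CT analysis added nothing to the FRAX form.

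**The case against.** The abstract sentence gives all three rates and carries the attrition condition. It can be read as a compressed account of the three-arm calculation at 280 participants, the figure above 84%. The power section labels its tests accurately and claims nothing for PHOENIX against active control. The 4.8 points is derived as an expected effect, with no power attached, so the fault there is one misused term. Treatment initiation is a secondary outcome of a feasibility study, and nothing in the article says that a superiority or futility conclusion will be drawn from this contrast.

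Most of this stands, and it limits the point to wording. It does not remove it. The abstract still claims power for a superior rate over active control. The sample size section says treatment rates were used to set the target so as to give sufficient power for comparisons across arms. The term it applies to 4.8 points is wrong by a factor of about three.

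Three stronger readings are tempting but not supported:

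- *The powered test is not the planned one.* Logistic regression with arm as a factor gives the two-degree-of-freedom test; with arm as an ordered score it gives the trend. The article does not say how arm is coded and may leave that to a fuller plan.
- *The abstract claims 96% power.* It quotes no figure, and its attrition condition corresponds to the figure above 84%.
- *The power section's arithmetic is wrong.* It reproduces.

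**Conclusion.** The point holds as an overstatement in the abstract and in one term of the sample size section. PHOENIX versus active control has about 17% power with all 375 participants and 14% after the assumed attrition. The detectable difference at 80% power is about 15 to 17.5 points, not 4.8. The published power concerns the three-arm trend and the overall test, neither of which can show that PHOENIX is superior to active control.

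The results rest on the article's assumed rates, equal arms, a two-sided 5% level, unadjusted normal approximations and attrition spread evenly over the arms. The rounded rates and a one-sided test leave the conclusion unchanged. The randomisation target of 375, the 75% retention target and the conduct of the study are not affected.

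**What to change.** 1. **Abstract:** say that the power is for the three-arm trend or overall test of treatment rates at 20%, 16% and 5%, and remove the suggestion that superiority over active control is powered. A blanket claim of adequate power against usual care should also be avoided, because active control versus usual care falls to 71% after attrition.
2. **Sample size section:** call 4.8 points the anticipated difference.
3. **Power for treatment proportions:** keep the existing figures and add power by contrast, with the post-attrition value in brackets: PHOENIX versus usual care 97% (91%), active control versus usual care 83% (71%), PHOENIX versus active control 17% (14%).
4. **Predefined statistical analysis plan:** state that PHOENIX versus active control will be reported as an estimate with a 95% confidence interval (expected half-width 9.5 to 11 points), and that no conclusion about its superiority to active control will be drawn from the trend or overall test.

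The cost is a few sentences and a less favourable power statement. No extra participants or data are needed.

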**Ethics and dissemination:**

Approved by committee (National Research Ethics Service) East of England (EE) as REF/19/EE/0176. Dissemination will be through the Royal Osteoporosis Society (to patients and public) as well as to clinician peers via national and international bone/rheumatology scientific and clinical meetings.

**Trial registration number:**

ISRCTN14722819.

Strengths and limitations of this studyFirst osteoporosis screening study involving patients attending radiology CT waiting areas.Individuals randomised to either comprehensive screening for osteoporosis (by applying Fracture Risk Assessment questionnaire, CT bone densitometry and CT vertebral fracture detection) or usual care.Allows patients the flexibility to self-consent, and tests both the willingness of CT attenders to consent, CT technologies and information flow between trial centres and Cambridge hub.Limited by an amendment of the primary outcome measure because recruitment during COVID-19 pandemic predicted skew towards the more seriously ill (via cancellation of non-urgent and routine scans).Modifications to both the retention outcome and longer recruitment window were made to take account of pandemic redeployment of medical research team.Missing a secondary care direct intervention arm, which would relieve some of the burden from primary care to enact osteoporosis treatments.

## Introduction

Older patients attending hospital for CT scans may have undiagnosed spine fractures or low bone density and therefore stand to benefit from osteoporosis screening. Timely diagnosis and treatment of osteoporosis benefits many patient outcome domains (pain, quality of life, morbidity and in the case of zoledronate treatment, mortality). An estimated 43% of patients >60 years of age undergoing CT scans (for abdominal and pelvic problems unrelated to their bones) were found to have osteoporosis or vertebral fractures when scan images were examined using computer-analysis methods.^1^ However, radiologists reviewing CT scans reported only 16% of vertebral fractures in routine practice,^2^ and bone mineral density (BMD) is rarely calculated from CT scans (CT BMD). This is despite CT BMD being approved internationally for the diagnosis of osteoporosis. Also, femoral neck BMD from CT is interchangeable with standard dual energy X-ray absorptiometry (DXA) BMD when using the global individual fracture risk web calculator Fracture Risk Assessment (FRAX). Indeed, several approved software packages now allow accurate diagnosis of osteoporosis in the hip and spine from routinely acquired CT images, while at the same time facilitating vertebral fractures identification and grading.

Systematic reviews indicate that overlooking osteoporosis or vertebral fractures can lead to serious, preventable pain, disability and health costs (>£2 billion per year from osteoporosis in the UK).^3^ Osteoporosis is a common disease in older women and men: osteoporosis is associated with >200 000 vertebral fractures and >85 000 hip fractures annually in the UK.^4^ Osteoporosis-related fractures have a high morbidity and, despite low cost-effective treatments, women and men are increasingly presenting at clinics with advanced multiple vertebral fractures, loss of body height, compressed abdominal contents, dysphagia, severe and chronic pain and reduced mobility. Despite an ageing UK population, osteoporosis remains underdiagnosed and undertreated.^5^ The osteoporosis case-finding rate in primary care is low and there is no national mandate for screening. High-risk patients may be referred for DXA and are offered treatment if fracture risk is sufficiently high. Vertebral fractures are infrequently detected in usual care even though they (alongside hip fractures) cause the biggest burden to patients and the health service. We hypothesise that targeted screening will improve on usual care and improve diagnosis. The Picking up Hidden Osteoporosis Effectively during Normal CT Imaging without additional X-rays (PHOENIX) intervention is a simple and widely practicable intervention to facilitate osteoporosis identification, diagnosis and treatment in patients attending for routine clinical CT at any hospital. It has been developed to apply software to CT scan images and repurpose them for measuring bone density, fracture risk and to identify crushed vertebrae.^6 7^ It couples timely diagnosis with an individualised report (built from a guideline-derived clinical decision tree) sent to general practitioners (GPs) containing advice on recommended investigations, National Institute for Health and Care Excellence (NICE)-approved, cost-effective treatment/lifestyle advice to reduce osteoporotic fractures.^8^ We expect benefits to accrue through early diagnosis and treatment of osteoporosis, with additional justifications for investigating this population shown in box 1. Preventing fractures could lead to decreased societal and social burden, and reduced healthcare and social care costs.

Box 1Opportunistic osteoporosis screening of CT scan attenders and rationale for Picking up Hidden Osteoporosis Effectively during Normal CT Imaging without additional X-rays (PHOENIX) interventionCT attenders are a high-risk population: >30% of older adults have undiagnosed vertebral fractures or osteoporosis that can be effectively treated once identified.^13^The PHOENIX intervention diagnoses osteoporosis on scans already undertaken, so there is no requirement for additional X-ray exposure or hospital attendance.The PHOENIX intervention can be applied to avoid the necessity of extra dual energy X-ray absorptiometry (DXA) visits and DXA reporting in multiple clinical scenarios, such as in the setting of radiology reporting quality improvement programmes that increase CT diagnosis of vertebral fractures, or to formally diagnose patients with osteoporosis after large-scale artificial intelligence (AI) vertebral fracture identification methods (eg, Optasia or ZEBRA AI1 tools).Screening is effective at reducing hip fractures. A recent trial of primary screening based on clinical risk factors and targeted bone density scanning reduced the hip fracture incidence by 28% over 5 years, with a number needed to screen (NNS) of 111 to prevent one hip fracture.^14^Systematic reviews of screening for osteoporosis suggest a NNS of 43 people (aged 75 years or over) to prevent one vertebral fracture.^15^Fracture risk is currently assessed opportunistically by general practitioners. Current advances in IT software could augment this practice to make more efficient and effective use of healthcare resources, as recommended by the National Institute for Health and Care Excellence, Clinical Guideline 146.^15^A 2013 study found that radiologists failed to report 84% of clinically important vertebral fractures from routine CT scans.^4^ However, once combined with new computerised analysis methods, CT scanners can effectively determine bone density and fractures.^7^There is a fourfold risk of another vertebral fracture occurring after the first one^16^ confirming the progressive nature of established osteoporosis.Generalisability: 1 million CT scans were performed in the UK in 1996, increasing to 5 million in 2016,^17^ permitting screening of many ‘at-risk’ patients. Interventions such as PHOENIX are not complicated, nor technically demanding for those hospital staff who routinely analyse DXA scans.

## Methods and analysis

This feasibility study aims to test our PHOENIX intervention, which begins by offering adults attending hospitals for CT (for any reason) a comprehensive bone health screen, followed by ‘opportunistic’ reuse of their CT scans for bone densitometry. The intervention ends with their GPs receiving detailed written advice on managing the participants’ bone health. Patients are offered an invitation pack comprising a novel informed consent form/data capture tool that the patient can fill out with or without assistance, and a participant information sheet. Specifically, we want to determine whether it is feasible for our team to undertake a large trial of the PHOENIX intervention to prevent fractures in a larger population of CT attenders. Hence, our co-primary outcome measure is our ability to randomise 375 ‘high-risk’ participants within 10 months. For the larger fracture prevention trial to be feasible, the other co-primary outcome measure must be achieved, which is retention at 12 months; our ability to record bone active treatment data (yes/no) in 75% of surviving patients. Power calculations for any future trial will be informed by the secondary outcome measure; the percentage of participants in each arm who have (i) received a treatment recommendation (due to osteoporosis, vertebral fracture or high FRAX risk) and (ii) received and commenced treatment 12 months after their CT scan. Box 2 contains a summary of the key features of the study protocol.

Box 2Summary of key features of the Picking up Hidden Osteoporosis Effectively during Normal CT Imaging without additional X-rays (PHOENIX) study protocolPragmatic featuresPatients attending CT waiting rooms are offered a PHOENIX invitation pack comprising a novel informed consent form/data capture tool to ascertain Fracture Risk Assessment (FRAX) score (online supplemental file 1) that the patient can fill out with or without assistanceThe intervention (tested in group 1) comprises (i) retrieving the CT scans of those ‘amber’ or ‘red’ risk individuals with moderate to high 10-year fracture risk by FRAX, (ii) hip and spine bone mineral density analysis with vertebral fracture assessment and (iii) sending the general practitioner (GP) guidance from a clinical decision tree.The intervention take place ‘behind the scenes’ without impacting on patient flow or the radiography/radiology workflow.Data (imaging, clinical risk factor, Patient Identifiable Information (PID) including sensitive clinical information) flow via secure encrypted and approved methods including the NHS Image Exchange Portal, Picture Archiving and Communications System (PACS) and nhs.net secure clinical email.Technical staff can ‘pull’ clinical CT images for assessment at any time.Primary outcome measures/end pointsFeasibility of recruitment: defined as ability to randomise 375 ‘at-risk’ participants over continuous 10-month period.Retention: defined as retaining 75% of surviving participants to 12 months postrandomisation, proven by receipt of follow-up postal questionnaire (specifically an answer to the bone active medication received; yes/no question).Secondary outcome measures/end pointsNew vertebral fracture identification across three arms assessed at 12 months.Osteoporosis identification across three arms assessed at 12 months.Bone active medication initiation across the three arms assessed at 12 months.Survival at 12 months across three arms assessed at 12 months.Inclusion criteria: participants eligible for the trial should fulfil all of the following at randomisation:Attending for a routine clinical CT scan.Able to provide informed consent.Aged ≥65–90 years (women) or ≥75–90 years (men) attending for CT for any clinical reason, where the spine and/or hips are visible in scan images.Exclusion criteriaMetalwork in hips (due to streak artefact on the contralateral hip within CT).Known to be receiving prescription treatment for osteoporosis other than calcium/vitamin D (ie, bisphosphonate drug, strontium ranelate, denosumab, raloxifene or teriparatide since it would be futile to identify already known and treated osteoporosis).Prone CT scan (which cannot currently be processed by the software).Role of patients and the publicActively participated in the study design in focus groups within the project team.Assisted in the design of data collection tools, including the informed consent form and information leaflet.Provided guidance on the acceptability of approaching participants in CT scan areas and insight into the anxiety of attending hospital among some more elderly members of society. Adding country of origin and ethnicity questions to consent form to facilitate FRAX.Impact of COVID-19 pandemicRecruitment had to be paused due to the COVID-19 pandemic, then restarted in just one centre without face-to-face contact with patients. Therefore, recruitment was either by clinical approach/discussion versus self-consent based on just handing out recruitment packs after COVID-19 restrictions were brought in.

10.1136/bmjopen-2021-050343.supp1Supplementary data

The PHOENIX study is a parallel three-group, non-blinded randomised controlled study of volunteers aged ≥65–90 years (women) or ≥75–90 years (men) attending for CT for any clinical reason, where the spine and/or hips are visible in scan images. Specifically, CT-attending patient volunteers who have an elevated 10-year fracture risk (within the amber or red zones of the UK FRAX graphical outputs for further action) are randomised to one of three groups. The three arms allow comparison between (1) the PHOENIX intervention, (2) an alternative active control ‘middle’ group (to assess whether GPs will investigate or treat patients based solely on receipt of a populated FRAX questionnaire) and (3) a control (‘usual care’) group where no action is taken. Potential participants are identified ahead of attendance by the clinical or research team reviewing CT lists. Those eligible by age, sex and region of the body being scanned are handed the PHOENIX pack while attending the CT department. The specially designed informed consent form (online supplemental file 1) first guides the potential participant through eligibility screening questions (*Do you take medication for your bones once a week that requires you to sit or stand upright? Do you have a yearly infusion (drip) or injection for your bones? Do you have a hip replacement? Have you ever had a hip operation?*). If there is an affirmative answer to any of these questions, individuals are asked to return their forms and go no further. Those individuals who answer ‘no’ to all the questions are asked to supply key demographic data: date of birth, height, weight, country of origin and ethnicity (needed for accurate FRAX calculation) and National Health Service number (receptionists support the patient as needed with the latter). Individuals are also asked to document the reason for their scan, if they know it.

On the last page of the consent form, the eight validated bone health-relevant questions from the FRAX questionnaire are completed, along with patient address, telephone number, GP name and GP address. Completed paperwork is scanned and sent by email attachment within the national, clinically secure NHS.net email account infrastructure to our [name] address (except for local patients where the paperwork is collected directly from the CT reception). FRAX answers are processed by the research team at Cambridge who use the results to calculate the 10-year fracture risk score *without* femoral neck BMD online. Those at low risk of fracture (within the green zone of the UK FRAX graphical outputs) are not randomised, but for completeness, these low-risk participants do eventually have the bone parameters in their CT scans reviewed. CT scans from participants in this ‘green’ category are retrieved later and put through the PHOENIX intervention 13 months after they consented, allowing the study team to ascertain whether FRAX had been effective in picking up patients with osteoporosis/high fracture risk in this CT waiting room setting. Those in the remaining ‘red’ and ‘amber’ risk categories are randomised to one of three arms, described below: group (1) the PHOENIX intervention, (2) active control (FRAX questionnaire results only sent to GP) and (3) usual care. The flow of patients through the study, including randomisation is shown in figure 1.

